### Recruitment and Informed Consent or Assent

The children are recruited from public schools, however heterogeneity in terms of socio-economic background is inevitable in the South African context. The Principal Investigator received endorsement and approval from the Department of Education to approach the school principals to present the project and discuss the details of each measurement and the purpose of the study. A school teacher, not directly involved with the particular children, will be identified as the mediator. Handout letters are circulated to the parents/caregivers to indicate their participation. Parents are invited to address any questions to the research team in order to make an informed decision and give parental permission for their child to participate in the study. All the relevant documentation including an informed consent/assent will then be provided to interested families. When the child along with the parents agree to participate, they will be requested to complete the informed consent/assent forms along with a battery of questionnaires prior to participation, and provide further consent/assent on the day of measurements.

## Data Collection

### Blood Pressure

To reduce inter-observer variability, validated (34, 35) and automated oscillometric pediatric blood pressure monitors [Omron HBP-1100-E, (OMRON Healthcare Co., Ltd. Kyoto, Japan)] will be used. The participants are requested to have avoided stimulant drugs or foods (self-reported), to sit quietly for 3–5 min with his or her back supported, feet on the floor and right arm supported, and the cubital fossa at heart level, before the blood pressure is measured (36, 37). The right arm is preferred in repeated measures of blood pressure for consistency and comparison to standard tables and because of the possibility of coarctation of the aorta, which might lead to false (low) readings in the left arm (38). Appropriately sized cuffs will be fitted for each child. Blood pressure measurements will be taken five times consecutively with 1-min resting intervals. The mean of the three measurements with the smallest variation will be used to calculate a mean for further analysis (22).

### Pulse Wave Analysis

Arterial pulse wave analysis will be performed using validated oscillometric Mobil-O-Graph monitors (I.E.M. GmbH, Germany) with integrated ARCSolver software (39, 40). The Mobil-O-Graph monitors are programmed to perform pulse wave analysis in duplicate after which the data will be downloaded for each participant using the HMS Client-Server software package Version 4.7.1 (I.E.M. GmbH, Germany). The participants will be fitted with an appropriately sized cuff for mid-upper right arm circumference in a sitting position. According to one measurement of brachial blood pressure, two measurements will be taken during the diastolic pressure for pulse wave analysis (pressure sensor MPX5050, Freescale Inc., Tempe, AZ, USA). This method determines parameters such as the central systolic blood pressure and central pulse pressure, the augmentation index and the standardized augmentation index at a heart rate of 75 beats/min, stroke volume, cardiac output, total vascular resistance, and aortic pulse wave velocity.

### Retinal Vessel Analysis

Static retinal blood vessel images will be captured using a Static Retinal Vessel Analyzer (SVA-T, Imedos Systems GmbH, Jena, Germany). The system consists of a fundus camera (Topcon TRC NW8) and analyzing software (Visualis 2.80, Imedos Systems GmbH, Jena Germany), allowing non-invasive and non-mydriatic assessment of retinal vessel diameters. Two valid images from the retina of both the left and right eye with an angle of 45° and with the optic disc in the center are taken per child. Retinal arterioles and venules, coursing through an area of 0.5–1 disc diameter from the optic disc margin, will semi-automatically be identified at higher magnification using the Vesselmap 2, Visualis, Imedos Systems GmbHsoftware. The examiner will differentiate all retinal arterioles and venules in the outer ring-zone and measure them with the software tools. Vessel diameters will be averaged to central retinal artery (CRAE) and vein equivalents (CRVE), using the Parr-Hubbard formula (41) and the arterio-venous ratio (AVR) will be subsequently determined (CRAE/CRVE). For the CRAE and CRVE we will use the mean of the right and the left eye results. Vessel diameters will be presented in measuring units (mu). In the model of Gullstrand's normal eye, 1 mu relates to 1 μm.

### Anthropometry and Bioelectrical Impedance Analysis

Anthropometric measures of height (cm) and weight (kg), waist circumference (cm), and skinfolds will be measured according to the International Society for the Advancement of Kinanthropometry (ISAK) procedures (42). Body mass is taken without shoes with the children dressed in light clothing with a Seca 813 digital scale to measure weight to the nearest 0.1 kg, and stature with a Seca 213 stadiometer (Birmingham, United Kingdom) with a perpendicular board to the nearest 1 mm. We will measure waist circumference consecutively in triplicate with a Lufkin® Executive thinline 2 mm steel tape (Apex Tool Group B.V.; AK Emmen, Netherlands) to the nearest 1 mm. Skinfolds of the triceps (measured parallel to the long axis of the arm at the triceps skinfolds site), and the subscapular (measured with the fold running obliquely downwards at the subscapular skinfold site) skinfolds, will be taken with a Harpenden skinfold caliper (Holtain Limited, U.K.) with a constant pressure of 10 g/mm^2^ to the nearest 0.2 mm. Skinfolds and waist circumference are carefully located using the correct anatomical landmarks. The sum of the triceps and subscapular skinfolds will be used to calculate the percentage body fat using the equations recommended for use in children from different settings (43).

Body composition will also be assessed using bioelectrical impedance analysis. The bioelectrical impedance analysis will be performed once using the Bodystat 1500® MDD (MultiScan 5000, BodyStat, Ltd). The bioelectrical impedance analysis detection electrodes are placed at the pisiform prominence of the right wrist and the anterior surface of the true ankle joint (44), which pass an imperceptible alternating current (frequency 50–60 hz) from one to another, measuring the impedance. A 200 g weight adjustment for clothing is applied. Measurements are conducted at a similar time of the day, after overnight fasting. Data from the bioelectrical impedance analysis include total body water, fat-free mass, lean body mass, body fat percentage, and total body fat in kilograms. Additionally, the bioelectrical impedance also provides data for impedance (Ω), resistance (Ω), and reactance (Ω).

### Physical Fitness

Prior to physical fitness tests, the children will perform a standardized 5-min warm-up. The test battery consists of a 20 m shuttle run (endurance), a 20-meter speed test (running speed), jumping sideward (coordination and agility), standing broad jump (strength), balancing backwards (balance), jumping, catching, kicking, and running (motor skill competences and coordination). All the tests will be performed during school time in the morning at the school with the same standardized equipment.

The following physical fitness tests are included:

The *20 m shuttle run* is a validated test measuring cardiorespiratory fitness by running back and forth in a 20 m distance (45). The initial running speed is set at 8.0 km/h with an increase of 0.5 km/h every minute, paced by beeps on an audio system. The maximal performance is achieved when the child did not cross the 20 m line at the moment of the beep for two consecutive 20 m distances. Numbers of “stages” achieved (1 stage ≈ 1 min) are counted with a precision of 0.5 stages (46). Participants are given a warning if they did not reach the line in time with the audio signal, and the test is ended if the participants could not reach the line for two successive shuttles or if the participant stopped voluntarily. But over and above this, the participants are verbally encouraged to perform maximally during each assessment and to run the test barefoot.The *20 meter speed test* is measured using a 20-m sprint (47). Time is assessed by electronic timing gates of the Smart Speed testing device with a precision of 0.01s (HL2-31, Tag Heuer, La Chaux-de-Fonds, Switzerland). The start follows an acoustic signal. The faster of the two trials will be further analyzed.Coordination or agility and muscular endurance are measured with the *jumping sideward* test (48). The children jump repeatedly, as many times as possible, within 15 s, with both legs together on alternating sides of a wooden strip. Five single test jumps will be performed per child prior to testing. This task is performed twice as fast as possible. The sum of the two trials are taken for the analysis.Using a *balancing backwards* test on 3 m long bars with a starting width of 6 cm, followed by 4.5 and 3 cm, respectively, dynamic balance will be measured (48). Children are allowed to balance once forward and once backwards over the widest bar for familiarization. The number of steps until the child's foot touch the floor is counted. Three trials are performed for each bar width. The sum of these nine trials will be used for analyses.The *standing broad jump* is designed to measure explosive strength (muscular fitness) and expressed in centimeters (cm) (49). Two trials will be given and the best trial recorded in centimeters. This test is performed on a non-slippery mat designed specifically for standing broad jump.*Motor skills:* Competence in catching, kicking, running and jumping are assessed qualitatively and quantitatively. The Test of Gross Motor Coordination-2 (TGMD-2) (50) will be used to assess competence in each motor skill qualitatively. After demonstration by the tester, two attempts of each skill are performed and scored according to specific sub criteria for each skill (0 = no mastery, 1 = mastery), and then summed to obtain a competence score. A quantitative measure for each motor skill will also be determined. Catching and kicking accuracy are additionally scored out of 5 attempts, also using the TGMD-protocol (distances between testers and to the kicking target of 1.5 cm wide), while the distance jumped in the standing broad jump (49) and the time to complete the 20-meter speed test (47) will be used as quantitative measures for speed and jumping.

### Physical Activity Using Accelerometers

Physical activity will be further assessed using the ActiGraph GT3X (model 7164; Fort Walton Beach, FL, USA), which uses a solid-state triaxial accelerometer. The vertical axis is used as the cut-points and equations included for testing are determined based on accelerometer counts from the vertical axis. Before each experiment the accelerometer is initialized to collect data in 15-s epochs. Trained research assistants will fit the ActiGraphs on elasticized belts worn at the waist (just over the anterior superior iliac spine), according to manufacturer's instructions. The monitors are set to collect data in 30-s time increments for a time period of seven full days. Participants will be instructed to wear the waist-worn accelerometer 24-h/day for seven consecutive days. However, they are permitted to remove the accelerometers if they feel uncomfortable wearing the device during sleep. The participants will be advised to remove the accelerometers only during water-based activities such as bathing or swimming. Accelerometer data will be downloaded from the device to the computer using the ActiLife 6 Single (inc. 1 Full & 5 Lite activations) software. ActiGraph output data will be used as 15-s epochs or converted to 60-s epochs depending on the cut-point used. ActiGraph data will be classified as sedentary behavior (SB; <1.5 METs), light physical activity (LPA; 2.0 and ≤ 3.0 METs), or moderate to vigorous physical activity (MVPA; >3 METS) using ActiGraph cut-points.

### Questionnaires

#### General Health and Demographics Questionnaire

Socio-demographic information, including data on personal (age, sex, ethnicity) and family information (i.e., education of the parents, employment, type of dwelling, household amenities and marital status), as well as family history of cardiovascular disease, will be collected by means of a standard General Health Questionnaire. Parents are requested to assist in providing this information.

#### Physical Activity Questionnaire

A six-item questionnaire was developed and validated for completion by parents to provide information on their child (51). This questionnaire is self-administered, and will be sent home to the parents for completion and then sent back to the school on the day of study participation. The six questions included the usual amount of time per day spent in sleeping, naps, and various indoor and outdoor activities, which are grouped according to physical activity intensity (sedentary, moderate, and vigorous). From the information provided by parents through the questionnaire, the amount of daily time spent in different intensities of physical activity will be computed in minutes and as a percentage of time at home. Sports and supervised activities are recorded weekly and computed to minutes/day of different physical activity levels according to the reported activity. One additional question is asked to assess parents' overall perception of the child's typical physical activity level by assigning it to one of the three categories ranging from 1 (inactive) to 3 (very active).

#### Healthy and Unhealthy Food Intake Survey

We developed a simplified food frequency questionnaire to collect data on the consumption frequency of healthy and unhealthy food groups. The food groups included reflect foods reported to be eaten by South African school children and included four groups of healthy foods (fruits, vegetables, milk, meat/fish/poultry/eggs) and six groups of unhealthy foods (cold drinks, sweetened hot drinks, sweets, salty snacks, cakes and fast foods) (52, 53). This questionnaire is based on a questionnaire that was used in the WHO Global school-based student health survey (GSHS). The GSHS questionnaire concentrated on four food groups, fruits, vegetables, carbonated soft drinks and fast foods (54). Collection of reliable and accurate data on the dietary intake of young children is a challenge, therefore only intakes of different food groups were considered (55). A recent study showed that four dietary items of the School Physical Activity and nutrition questionnaire were sufficient to present a robust variable consistent with a healthy eating pattern (56). A similar questionnaire listing five healthy food groups (fruits, vegetables, legumes, fish, meat) and five unhealthy food groups (cold drinks, cookies, cake, candies, “ice pop”) with five different responses of frequency of intake was used to determine intakes of healthy and unhealthy foods of African children in Burkino Faso (57).

The face validity of the questionnaire has been assessed among Nutrition scientists with experience in dietary assessment. The scientists approved the questionnaire, but made recommendations about adding processed meat to the fast food group. This recommendation was implemented in the final questionnaire used in this study. The questionnaire was then pilot tested for comprehension in a group of caregivers of 6–8-year old children and was found to be easy to understand and complete. Healthy foods were defined as foods containing essential nutrients for child growth and general health, namely fruits, vegetables, milk, meat/fish/poultry/eggs (57). Unhealthy foods were defined as foods that provide energy, sugar, salt and fats, but do not make an important contribution to essential nutrient intake (54). A colored picture file with examples of foods from each group will be presented with the questionnaire to facilitate responses. This questionnaire is taken home to be completed with the assistance of the parent or caregiver and the child involved.

The median frequency of intake of each food group will be calculated, and categorized frequencies of food groups will be presented. Outcome data of participants with low frequencies of each food group (0–2 times/week) will be compared to data of participants with high frequencies (5–7 times/week) of each food group.

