### Outcomes

The study has the following outcomes based on primary school children in the North West province of South Africa:

To evaluate obesity and hypertension prevalence along with its determinants motor skills and physical fitness/activity, intake from food groups, and psychosocial behaviors.To assess the association of body mass index and blood pressure with central pulse wave velocity and retinal vessel diameters in South African children.To identify whether the associations of arterial modulation with physical fitness/activity, intake from food groups, and psychosocial behaviors are dependent on ethnicity.

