### Proposed Analysis

#### Sample Size Calculation

We aimed to include 20 urban schools from the [name] district with a conservative calculation of 60 children participating per school, leading to a total sample size of ~1,200 children over a period of 19 months. However, with dropouts or school absentees we expected a total sample size of ~1,000 participants. Using G^*^Power version 3.1.9.2 (62), we determined the required effect size (*f*
^2^ = 0.025) for a given 2-sided level alpha error of probability at 0.05, in a total sample size of 1,065 and ten predictors for fixed model linear multiple regression analysis with blood pressure or pulse wave velocity or arteriolar-to-venular-ratio as main outcomes. With the proposed sample of 1,065 children, we achieve 95.3% power.

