#### Statistical Analysis

The IBM^®^ SPSS^®^ Statistics software (Armonk, NY: IBM Corp.) will be used for data analysis. The 95% confidence intervals will be presented for measures of effect to indicate the amount of uncertainty. For future analysis, normality will be assessed by visual inspection using normal QQ plots. If residual plots indicate deviation from model norms, logarithmic transformations of the outcome variables will be considered. To describe continuous characteristics, we will use median and interquartile ranges or means and standard deviations; and for binary variables, we will use percentages by performing chi-square tests. To estimate absolute changes in outcome variables for one unit increase of determining factors, multiple linear regression analysis will be applied.

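### The diet comparison of 0–2 with 5–7 times/week leaves out all children at 3–4 times/week without a reason and is not reconciled with the planned per-unit regression

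*Protocol article*

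**What the plan says.** The food survey covers ten groups: "four groups of healthy foods (fruits, vegetables, milk, meat/fish/poultry/eggs) and six groups of unhealthy foods". Its analysis is described at the end of the section Healthy and Unhealthy Food Intake Survey. The first part is descriptive: "The median frequency of intake of each food group will be calculated, and categorized frequencies of food groups will be presented". The second part compares outcomes between two groups: "participants with low frequencies of each food group (0–2 times/week) will be compared to data of participants with high frequencies (5–7 times/week"). This is done separately for each food group. Nothing is said about children at 3–4 times/week.

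Two other sections bear on the same data. The Outcomes section evaluates obesity and hypertension along with their "determinants motor skills and physical fitness/activity, intake from food groups, and psychosocial behaviors". The Statistical Analysis section gives the general model: "To estimate absolute changes in outcome variables for one unit increase of determining factors, multiple linear regression analysis will be applied". The Sample Size Calculation bases its power on that type of model, "in a total sample size of 1,065 and ten predictors for fixed model linear multiple regression analysis".

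**The concern.** Diet is one of the study's main exposures. The only analysis written specifically for it uses the two ends of the frequency range and gives no estimate per unit of intake. The general model does give a per-unit estimate, but the article does not connect the two. An analyst could follow either section and report a different estimate, from a different set of children, on the same data.

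Three things are at stake:

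- **Precision.** Children at 3–4 times/week contribute nothing to the contrast, and all frequencies within an arm count as equal.
- **Shape.** A two-group difference cannot show how the outcome changes over the range of intake.
- **Comparability.** A child left out for fruit may be included for fast food, so the ten contrasts rest on ten different subsets. The third outcome asks whether associations depend on ethnicity, and leaving out the middle group thins those comparisons further.

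**Working it through.** **1. The plan's own power figure.** Inputs from Sample Size Calculation: f² = 0.025, alpha 0.05, ten predictors, N = 1,065, stated power 95.3%. For the overall F test the noncentrality is λ = f² × N = 0.025 × 1,065 = 26.6, with 10 and 1,054 degrees of freedom. The result is 96.6%, and 95.35% at N = 1,000. The stated figure is therefore reproduced to within 1.3 points as a joint test of ten predictors. A test of a single coefficient at the same f² would give 99.9%. So 0.025 is best read as the effect of ten predictors together, and one food group may account for less.

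**2. Information kept by the contrast.** Assume integer frequencies 0–7 and a linear relation. Let p_L and p_H be the shares of children in the low and high groups, d the difference in their mean frequencies, and Var(X) the variance of frequency over all children. Then

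Relative efficiency = [d² × p_L × p_H / (p_L + p_H)] / Var(X).

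- *Uniform over 0–7:* p_L = p_H = 0.375, d = 6 − 1 = 5, Var(X) = 5.25. This gives 25 × 0.1875 / 5.25 = 4.6875 / 5.25 = 0.893.
- *10% at 3–4, the rest split evenly:* p_L = p_H = 0.45, Var(X) = 6.25. This gives 25 × 0.225 / 6.25 = 0.90.
- *40% at 3–4, one fifth of the rest low:* p_L = 0.12, p_H = 0.48, Var(X) = 3.44. This gives 25 × 0.096 / 3.44 = 0.70.

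The last two are the ends of an assumed grid: 10–40% of children at 3–4 times/week (roughly 106 to 426 of 1,065), with the low group making up 20–50% of the rest and frequencies equally likely within each band. Over this grid the contrast keeps about 70–90% of the information.

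With binomial(7, p) intake, the efficiency is 0.85 at p = 0.5 (55% of children at 3–4), 0.62 at p = 0.4 (48%) and 0.27 at p = 0.3 (32%). In the last case the high group is very small.

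**3. Power.** The table compares a one-degree-of-freedom slope on all 1,065 children with a two-sample comparison of low against high, two-sided 0.05.

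| Partial f² of one food group | Slope, all children | Low vs high, grid | Low vs high, binomial p = 0.5 / 0.4 / 0.3 |
|---|---|---|---|
| 0.0075 | 80.6% | 65.5–76.4% | 74.0 / 60.7 / 30.9% |
| 0.010 | 90.3% | 77.7–87.2% | 85.2 / 73.1 / 39.3% |
| 0.025 | 99.9% | 99.0–99.8% | 99.7 / 98.3 / 76.1% |

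Over the grid the loss at f² = 0.0075 is 80.6 − 76.4 = 4.2 to 80.6 − 65.5 = 15.1 points. At 0.025 it is 0.1 to 0.9 points.

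**4. If the relation is not linear.** Take uniform intake and an effect that appears as a step at 5 or more times/week. The contrast carries 0.375 × 0.375 / 0.75 = 0.1875 units of information. The linear term carries Cov² / Var(X), where Cov = 18/8 − 3.5 × 0.375 = 0.9375, so 0.9375² / 5.25 = 0.167. Here the contrast is about 12% more efficient (0.1875 / 0.167). The gain from a linear term therefore depends on the relation being near linear.

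**The case against.** The strongest case on the other side is that a group comparison and a regression can coexist. A reader might infer that diet will be analysed only by low against high, with the middle group discarded from the study. The article does not say so. Outcomes and Statistical Analysis together point to a per-unit regression on determinants, which would keep every child if intake enters as a number. The children at 3–4 times/week also remain in the medians and categorised frequencies. This stands, and it limits the point to one unexplained omission and one missing link between two sections.

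The size is also open to challenge. The article does not give the questionnaire's response options; it mentions only that a similar instrument used five. The 0–7 integer scale, the intake distributions and linearity are all assumed here. At the plan's f² the loss is small in most scenarios, and under a step effect the contrast does better. This stands too, so the figures are ranges and not estimates.

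Three further inferences are tempting but unsupported:

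- **The stated power is wrong for the diet contrasts.** The Sample Size Calculation ties its figure to the multiple regression and claims nothing for low against high.
- **The contrast is unadjusted.** The article is silent on this, and a condensed article may leave covariates to a fuller document.
- **Ten food groups by three outcomes give a 79% chance of a false positive.** That is 1 − 0.95³⁰ = 0.785. It needs 30 independent tests with no true effects, and measures on the same children cannot be presumed independent.

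What the objection does not answer is why 3–4 times/week is left out, or which of the two analyses carries the dietary result.

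**Conclusion.** The point holds in a limited form. The survey section fixes a comparison that omits every child at 3–4 times/week, a different subset for each of ten food groups, and gives no reason. It is not reconciled with the per-unit regression, although food-group intake is named as a determinant.

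Under a roughly linear relation the contrast loses about 10–30% of the information over the assumed grid, and up to about 73% (1 − 0.27) in the most skewed shape tried. In power, this is about 4–15 points for an effect with about 80% power in all children. It is under one point at f² = 0.025 over the grid, though power falls to 76.1% in the most skewed shape. No single figure follows from the documents. The lack of reconciliation does not depend on any of these assumptions.

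**What to change.** In Healthy and Unhealthy Food Intake Survey and in Statistical Analysis, state that:

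- intake frequency of each food group enters the multiple linear regression for all children, as a numeric or ordered term according to the questionnaire's response options;
- non-linearity is checked, for example by comparing the fit with one that treats frequency as categories;
- this regression is the main dietary analysis, and low versus high is a descriptive or secondary comparison.

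This takes about two sentences and uses the same data. The cost is a linearity assumption, which the check covers. If the omission of 3–4 times/week was deliberate, the reason should be stated next to the comparison.
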